## 7.5 Concomitant Medication

Within 0-30 days, actively follow up and observe the local and systemic adverse events of the subjects and record them on the vaccination diary card. At the same time, it is necessary to record the drug used of the subjects in the vaccination diary card.

**Medication Allowed:** During the clinical trial, if the subject has adverse events, necessary medication and medical treatment should be allowed.

**Vaccines Allowed:** Other vaccines are allowed during the trial, which should be carried out 14 days after the trial vaccination. Emergency vaccination, such as rabies vaccine and tetanus vaccine, is not restricted.

**Medication Record:** To understand the influence of drug use during the trial on vaccine safety and immunogenicity, and to collect adverse events that may be related to vaccination without omission, investigators should instruct the guardians of the subjects to record the medical treatment and medication in diary cards as much as possible and assist in collecting the hospitalization medication records of the subjects during the observation period. When SAE occurs, copies of corresponding medical records and medication records should be collected and kept. The following drugs need to be transcribed into the electronic case report form (eCRF).

- (1) Hormone/steroid drugs and other immunosuppressants.
- (2) Antiallergic Drugs
- (3) Antipyretics/analgesics/NSAIDs
- (4) Prophylactic Vaccines
- (5) Therapeutic Medical Products
- (6) Antibiotics
- (7) Antiviral Drugs
- (8) Chinese Patent Drugs
- (9) Others

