#### **4.3.3 Immune Persistence Endpoints:**

GMT of anti-SARS-CoV-2 neutralizing antibody and IgG antibody, the proportions of neutralizing antibody titered  $\geq 1:16$ ,  $\geq 1:32$  and  $\geq 1:64$  at 3 months, 6 months, 9 months and 12 months after full course of immunization,

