## **7.3 Safety Observation and Follow-up**

### **7.3.1 Safety Observation**

(1) Observe the site for 30 minutes after vaccination to collect local and systemic adverse events.

(2) Telephone follow-up once in 6-24 hours after vaccination, within 1-3 days and 4-7 days respectively, the subjects were followed-up by telephone and guided to observe the adverse events

correctly and fill in the diary card.

(3) On the 14th day (Visit 4), the investigator reviews the filling of the diary card during this period and re-collect the diary card.

(4) On the 8th -30th day after vaccination, the investigator uses telephone follow-up once a week, combined with active report of the subjects to monitor the safety.

(5) When it is known that the subject has adverse reactions/events of Grade 3 or above, a face-to-face visit should take place within 24 hours.

(6) SAEs and AESIs are observed from the first dose to 6 months after the full course of vaccination by means of monthly telephone follow-up and self-reports from the subjects.

Note: Subjects should report respiratory tract infection symptoms such as fever and cough. Investigators should make comprehensive judgments, carefully identify whether it is common solicitation symptoms after vaccination or infection caused by other reasons, and closely observe the disease progress. Once the disease worsens, report it to the person in charge of the site quickly, and start the green treatment channel quickly to ensure that the subjects get timely diagnosis and treatment.

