| Observation at site after vaccination                     | ✓                                                                                       |                                                                                         |                                                                                           |                                                                                            |                                                                                            |                                                                                                    |                                                                                                    |                                                                                                    |                                                                                                     |
| Telephone follow-up after vaccination                                 | ✓                                                                                       | ✓                                                                                       | ✓                                                                                         |                                                                                            |                                                                                            | Once per month within D28-6M                                                                       |                                                                                                    |                                                                                                    |                                                                                                     |

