| Concomitant Medication                                                | ✓                                                                                       | ✓                                                                                       | ✓                                                                                         | ✓                                                                                          | ✓                                                                                          | ✓                                                                                                  | ✓                                                                                                  |                                                                                                    |                                                                                                     |
| Adverse events                                                        | ✓                                                                                       | ✓                                                                                       | ✓                                                                                         | ✓                                                                                          | ✓                                                                                          | ✓                                                                                                  | ✓                                                                                                  |                                                                                                    |                                                                                                     |

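### Other vaccines are permitted with no end date, but scheduled recording of vaccines and immunosuppressants stops at month 6, while persistence titres are drawn at months 9 and 12

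*Protocol*

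**What the plan says.** **Permission.** Section 7.5: "Other vaccines are allowed during the trial, which should be carried out 14 days after the trial vaccination". It adds: "Emergency vaccination, such as rabies vaccine and tetanus vaccine, is not restricted". No end date is set and no type of vaccine is excepted. The limits elsewhere are narrower. Section 5.1.3 makes receipt of another investigational vaccine a reason for withdrawal, the list of protocol violations repeats this, and the list of deviations concerns only too short an interval to another vaccine.

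**Recording.** Section 7.5 gives the influence of drug use on safety and immunogenicity as a reason for recording medication. It lists immunosuppressants and steroids, and prophylactic vaccines, among the items for the eCRF. It also asks investigators to "assist in collecting the hospitalization medication records of the subjects during the observation period", without defining that period. In Table 4 the row "Concomitant Medication" is ticked at V1 to V7 and blank at V8 and V9. Telephone follow-up is "Once per month within D28-6M". The diary card goes back at Visit 4, when "the investigator reviews the filling of the diary card during this period and re-collect the diary card" (section 7.3.1).

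**Endpoints.** Section 4.3.3 names GMTs and the proportions at three titre thresholds "at 3 months, 6 months, 9 months and 12 months after full course of immunization". Table 4 ticks both antibody tests at V8 and V9. The Immunogenicity Persistence Set (IPS) in section 10.2 requires a blood sample and valid antibody data and nothing more.

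**The concern.** The protocol says why these exposures should be recorded and then schedules no recording before the last two of its four persistence draws. A subject who receives an authorised COVID-19 vaccine in months 7 to 12 breaks no stated rule, remains in the IPS, and contributes a titre that reflects the later vaccine as well as the trial dose. An immunosuppressant started in that period could move the titre the other way.

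At stake is a secondary objective, immune persistence. Equal uptake in the two arms would overstate absolute persistence in both. Unequal uptake would also shift the comparison between them. Equal uptake cannot be taken for granted late in the trial, since section 9 has the database locked and unblinded once the day 28 results are in, although it does not say that subjects are told their assignment.

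A statistical analysis plan can define how titres after such an event are handled. It cannot supply events that were never scheduled for collection.

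**Working it through.** **Step 1: schedule against endpoints (Table 4, section 4.3.3).**

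| Visit | Time | Concomitant medication | Monthly calls | Antibody tests | Persistence endpoint |
|---|---|---|---|---|---|
| V6 | 3 months | ticked | yes | ticked | yes |
| V7 | 6 months | ticked | end here | ticked | yes |
| V8 | 9 months | blank | no | ticked | yes |
| V9 | 12 months | blank | no | ticked | yes |

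Two of the four persistence time points have no scheduled question about vaccines or immunosuppressants since the previous visit. The adverse-event and SAE rows also stop at V7. The diary card is no substitute, having been returned at Visit 4.

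**Step 2: which exposures fall in the gap.** Investigational vaccines are covered by the withdrawal and violation rules. Vaccines such as rabies or tetanus should matter little for SARS-CoV-2 titres. What remains is authorised COVID-19 vaccines, immunosuppressants and steroids, and blood products or immunoglobulin.

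**Step 3: could the antibody data reveal a later vaccine?** Anti-N IgG is measured at V8 and V9, but every subject was primed with inactivated vaccine and half are boosted with it. A vaccine containing only spike antigen would not raise anti-N. It is not a reliable marker here.

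**Step 4: size, under assumed inputs.** The protocol has no figure of its own to reproduce. Let a share p of an arm have an unrecorded exposure that multiplies titre k-fold. On the log scale the arm mean rises by p × log k, so the arm GMT is multiplied by k^p.

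| k | p = 5% | p = 10% | p = 20% | p = 30% |
|---|---|---|---|---|
| 2 | 2^0.05 = 1.04 | 1.07 | 1.15 | 2^0.3 = 1.23 |
| 4 | 4^0.05 = 1.07 | 1.15 | 1.32 | 4^0.3 = 1.52 |
| 10 | not tabulated | 10^0.1 = 1.26 | 1.58 | 10^0.3 = 2.00 |

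If the exposed share differs between arms by p, with the same k, the GMT ratio moves by the same factor. A proportion above a titre threshold can rise by at most p, for example by at most 10 percentage points at p = 10%. The values of k and p are assumptions. They show how the bias behaves and do not predict it.

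**The case against.** The strongest reply is that blank cells in Table 4 do not amount to a rule that recording stops.

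- Section 7.3.2 has investigators ask about adverse events at on-site visits, with no end date.
- Section 11.8 lists concomitant medications among the data for the subject's file, section 11.2 has monitors review concomitant therapy, and section 12.1 calls for narrative notes on progress through the trial.
- The undefined observation period in section 7.5 could be read as reaching month 12.

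This has force: the text and the table are out of step, and a diligent site might ask anyway. None of these passages, however, schedules a question about vaccines or immunosuppressants at V8 or V9, and sites work from the schedule.

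Three stronger readings are tempting and are not supported.

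- A reader might infer that COVID-19 itself goes unrecorded after month 6. Section 8.2 asks for regular symptom follow-up, Table 4 note 5 allows PCR at any time for suspected symptoms, and section 7.4 provides blood sampling for suspected and confirmed cases. None of these ends at month 6. Symptomatic disease is at least partly covered, though section 8.2 is written around a first and second dose and nothing is ticked at V8 or V9.
- A reader might infer that every later COVID-19 vaccine is permitted. Investigational ones are not.
- A reader might infer that the data would be beyond repair. Vaccination is usually documented, sites check vaccination records at entry (section 7.2.1), and section 12.2 lets the investigator request medical records. Retrieval afterwards is possible, but it is not planned.

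**Conclusion.** The concern holds as a mismatch between section 7.5 and Table 4. Authorised COVID-19 vaccines and immunosuppressants taken after V7 have no scheduled capture, and the 9- and 12-month GMTs and titre proportions can be distorted as a result. The non-inferiority conclusions at days 14 and 28 do not depend on this, and at months 3 and 6 the exposures are scheduled for recording.

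The schedule gap is plain from the document. The amount of bias is not. It could be negligible (1.04-fold for k=2, p=5%) or large (2.0-fold for k=10, p=30%), and the protocol contains nothing that narrows this range. The point deserves correction because persistence is a stated objective and the correction is simple, not because material bias has been shown.

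**What to change.** Align Table 4 with section 7.5 by extending the concomitant-medication row to V8 and V9, limited to exposures that can affect titre:

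- any COVID-19 vaccine, with product and date;
- other vaccines;
- immunosuppressants and steroids;
- blood products or immunoglobulin.

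At the same visits, confirm any COVID-19 diagnosis since the last visit. Enter all of these with dates in the eCRF, so that titres drawn after such an event can be identified. Define the observation period in section 7.5 so that text and table agree. The change concerns data capture only and leaves the rules on permitted vaccines as they are.

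The cost is a few questions and one eCRF page at two visits that subjects already attend for blood, with no extra visit, sample or procedure.

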## 7.6 Criteria for Suspension or Early Termination

**In case of any of the following circumstances, the trial shall be suspended, and the investigator, the sponsor and the Ethics Committee shall jointly hold a meeting to decide whether to terminate the clinical trial early:**

- One case of Grade 4 adverse reaction related to vaccination or SUSAR in any group, including death or life-threatening SAE;
- The number of subjects with adverse reactions of severity Grade 3 or above

---

exceeds 15% of the subjects vaccinated in this subgroup;

- DSMB evaluation of clinical research has high potential safety risks.

**In case of any of the following circumstances, the clinical trial shall be terminated:**

- Sponsor has found that the vaccine has potential safety hazards or the trial has quality related problems, and requiring the complete termination of the study.
- The Ethics Committee requests the termination of the trial because of the violation of ethics in the trial.
- Request by the administrative authority to terminate the trial

## **7.7 Protocol Violation and Deviation**

### **7.6.1 Protocol Violations**

The list of protocol violations is as follows (including but not limited to):

- Fail of obtain subject's informed consent;
- Subjects who did not meet the inclusion criteria or met the exclusion criteria were enrolled in the study;
- Subjects received wrong research interventions (such as vaccination errors);
- Fail to report serious adverse events (SAE) within specified time;
- Received other investigational vaccines during the study period.

### **7.6.2 Protocol Deviations**

The list of protocol deviations is as follows (including but not limited to):

- Not receive the investigational vaccine during the window period;
- Not collect blood during the window period;
- The interval between vaccination and other vaccines is not long enough, except for emergency vaccination such as rabies.

## **7.7 Study Duration**

Eearly Subject Recruitment: 1 month;

Sequential Vaccination + immune persistence observation: about 18 months

Sample Testing: about 1 month

Complete the Summary Report: about 1 month

## **7.8 Site Closure**

All subjects completed long-term safety observation for 6 months after vaccination and blood collection for 12 months after immunization. All original data are collated, entered, and verified and submitted to the statistician. After clarifying the data after blind audit by the statistician, the study site is closed.

## **8. SAFETY DEFINITION, REPORTING AND MONITORING**

### **8.1 General Precautions**

This clinical trial is a randomized, double-blind and controlled trial design.

Before the start of the trial, the sponsor shall strictly examine the trial site in accordance with GCP requirements, focusing on whether the environmental facilities of the trial site meet the requirements of "Vaccination Management Standards" and "Guiding Principles for Quality Management of Vaccine Clinical Trials". Ensure the first aid facilities and first aid equipment in the first aid room are complete and effective, and the first aid doctors have corresponding qualifications and capabilities. Emergency related personnel (emergency doctors, emergency nurses, ambulance drivers, etc.) are trained to be qualified and familiar with the transfer routes and procedures of the agreed hospital. They are on standby at the trial site during vaccination. The trial site shall be equipped with ambulances. The ambulance shall be parked in a fixed position to keep the vehicle in good condition and in an emergency and shall be under the command and transfer of the emergency response team at any time. During the vaccination period, the agreement hospital will make daily preparations for medical personnel, instruments and equipment, first aid drugs and first aid sites to ensure that the subjects can receive timely treatment. The trial site shall formulate an emergency plan, stipulate personnel responsibilities, contact numbers, rescue routes and other measures to ensure timely handling of unexpected adverse events, and ensure effective contact between subjects and investigators so that any adverse events can be reported and handled quickly.

### **8.2 Risk Prevention Measures Related to COVID-19**

#### **(1) Trial site consideration**

Investigators during recruitment should confirm whether there are new COVID-19 cases or suspected cases in the same village/community by investigating or inquiring volunteers. Whether fever, dry cough, fatigue, nasal obstruction, runny nose, sore throat, myalgia, diarrhea, shortness of breath and dyspnea occurred recently;

#### **(2) Strengthen the management and personal protection of subjects during the study period**

Disinfection of each functional area of clinical research should be strictly done in the test site according to regulations, and windows should be opened and ventilated regularly. Strictly implement independent areas and special passages, and the recipients and their

accompanying personnel wait in relative divisions to avoid contact with people other than research doctors and nurses; All functional areas and public places should be equipped with hand disinfectants and temperature measuring devices, and recipients and their accompanying personnel entering the clinical research site should be equipped with masks to disinfect their hands and measure their body temperature.

The trial site shall strictly disinfect each functional area of clinical research according to regulations, and regularly open windows for air-ventilation. Strict implementation of independent areas and special passages, recipients and their accompanying personnel waiting in relative zones, to avoid contact with research doctors, nurses and other personnel other than research; All functional areas and public places should be equipped with hand disinfectants and temperature measuring devices. Recipients entering the clinical research site and their accompanying personnel are required to be equipped with masks to disinfect their hands and measure their body temperature.

During the first dose of inoculation, the on-site investigators shall remind the subjects to strengthen their own protection. If COVID-19 pandemic occurs locally, the subjects shall be provided with necessary protective materials such as masks, alcohol, etc. in time, and close attention to the health status of the subjects shall be drawn, especially the symptoms related to COVID-19.

### **(3) Detection of COVID-19 RT-PCR**

Subjects need to be tested for COVID-19 RT-PCR before first dose vaccination. PCR tests should be performed before 2nd dose vaccination, 14 days after 2nd dose, 28 days after 2nd dose, and regularly afterwards at the sites with permitted conditions. Investigators need to regularly follow up and track the subjects to identify whether they have developed fever, dry cough, fatigue and other symptoms recently. If the above symptoms exist, the subjects will be collected samples for etiological detection of SARS-CoV-2 according to the prevention and protection policy for COVID-19 and based on the symptoms of the subjects, or are advised to go to the hospital for blood testing and radiographic examination. If there are no symptoms such as fever, dry cough and fatigue, the subject should be home isolated according to the requirements of COVID-19 prevention and control protocol.

### **8.3 Handling and Reporting of Serious Adverse Events**

Serious adverse events refer to adverse medical events such as disability or loss of function, the need for hospitalization or prolonged hospitalization of subjects, and congenital abnormalities or birth defects.

Monitoring and reporting of adverse events in vaccine clinical trials are jointly completed by subjects, serious adverse event investigators, trial sites and responsible institutions at different observation time points with different stages.

The sponsor is the main body responsible for monitoring, evaluating and SAE reporting safety information of vaccine clinical trials. The person shall be designed as the administrator of clinical trial safety information monitoring and SAE reporting, and work with investigators to establish SOPs for clinical trial safety information monitoring and SAE reporting, know well the latest status of the safety information of the whole clinical trial, and timely report updates to all clinical trial institutions/ investigators and regulatory authorities.

If it is difficult to make a judgment on the correlation between SAE and vaccine or there is doubt about the judgment, when it is necessary to make a new judgment, the expert meeting shall make a judgment after argumentation.

